**Statistical analysis**

Data analysis will be performed using SPSS software on an intention-to-treat basis (significance level p < 0.05). Mean differences before and immediately after the interventions will be calculated. Baseline characteristics will be shown as mean ± standard deviation (SD) for continuous data including age, spherical equivalent, corrected distant and near visual acuity, accommodative response, pupil diameter, visual discomfort score and near work load. As for participants’ gender and the proportion of participants with changes, n (%) of male and female and n (%) of participants in each group will be shown as baseline characteristics. Only the results of the right eye were used in the statistical analysis. If the values were normally distributed, analysis of Covariance (ANCOVA) was used otherwise nonparametric test would be used for analysis. Chi-square test was used to compare categorical outcomes.

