**Background**:

Myopia is a public health problem worldwide, especially in some Asian countries like China, Singapore, and Japan.[^1^](#_ENREF_1) Chinese eye exercise, originating in 1963 with the theory of Traditional Chinese Medicine (Figure 1-4), is a kind of massage on acupuncture points around the eye to prevent myopia and alleviate visual fatigue.[^2^](#_ENREF_2) The exercise has been spreaded as a community ritual and living habit of primary and high school students for half a century in China. However, the prevalence of myopia in Chinese children increased remarkably in recent years.[^3-5^](#_ENREF_3) Therefore, the efficacy of Chinese eye exercise on preventing myopia or alleviating visual fatigue is widely questioned. Evidence from clinical trials of high level is needed to clarify that whether Chinese eye exercise is effective in slowing and preventing myopia progression, or at least in part in easing the symptoms related to myopia and visual fatigue.[^6^](#_ENREF_6)

[figure not shown]

Figure 1. Section 1 of Chinese eye exercises, massage on BL2 (cuanzhu)

[figure not shown]

Figure 2. Section 2 of Chinese eye exercises, massage on BL1 (jingming)

[figure not shown]

Figure 3. Section 2 of Chinese eye exercises, massage on ST2 (sibai)

[figure not shown]

Figure 4. Section 2 of Chinese eye exercises, massage on EX-HN5 (taiyang)

**Purpose**: To assess whether Chinese eye exercise is effective in altering accommodative lag, distant and near visual acuity, and visual symptoms in school-aged children in the short-term.

**Study type**: Interventional

**Study design**: Treatment, Parallel Assignment, Double Blind (Subject, Investigator, Outcomes Assessor), Randomized, Efficacy Study

**Estimated enrollment**: 180

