**Arms and Assigned Interventions:**

1. **Experimental**: **Standardized Chinese eye exercise**. The participants are trained with standardized Chinese eye exercise which contains accurate position of acupuncture points and appropriate pressure on the points.
2. **Sham comparator: Nonstandardized eye exercise.** The participants are trained with nonstandardized eye exercise performed on wrong positions where no acupuncture points at all.
3. **No intervention:** **Eye closure**. The participants are told to close eyes and don’t do eye exercise at all.

The locations of acupoints of standard Chinese eye exercises (SCEE) and sham point eye exercises (SPEE) are shown in **Appendix 1**.

To guarantee the performance quality of eye exercises, one independent investigator will first demonstrate the procedures of eye exercises and explain the principles for each child. Children will be asked to practice respective exercises under the instruction of the independent investigator for at least three times. During this period, mistakes will be repeatedly corrected until the children perform the eye exercises accurately. Finally, all participants’ performance quality of exercises will be assessed and scored by two independent judges. The assessment covered location, force, scope and frequency of the massage (**See Appendix 2**). Scores greater than 30/40 and differences between two judges less than 5 points were defined as qualified.

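### One p < 0.05 for three arms and no named primary contrast: a significant three-arm test need not mean that the standard exercise beats sham

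*Protocol*

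**What the plan says.** The Purpose paragraph of the protocol is "To assess whether Chinese eye exercise is effective in altering accommodative lag, distant and near visual acuity, and visual symptoms" in the short term. It names no comparator.

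Arms and Assigned Interventions defines three groups:
- **Experimental:** "The participants are trained with standardized Chinese eye exercise which contains accurate position of acupuncture points" and suitable pressure.
- **Sham comparator:** "nonstandardized eye exercise performed on wrong positions where no acupuncture points at all".
- **No intervention:** "The participants are told to close eyes" and not to exercise.

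Outcome measures defines the primary outcome as accommodative lag before and immediately after the intervention, with no between-arm comparison attached.

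Statistical analysis sets one threshold, "on an intention-to-treat basis (significance level p < 0.05", and one family of tests: ANCOVA if values are normally distributed, otherwise an unnamed nonparametric test. It gives no contrast, no testing order and no link from a test result to the stated purpose. The Study design line describes the trial as double blind and includes the subject among those blinded.

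**The concern.** The two control arms answer different questions. Standard versus sham isolates what correct acupoint position adds to rubbing the face. Standard versus eye closure mixes that with any non-specific effect of massage over rest. A trial can come out differently on the two, so the word effective in the Purpose has no fixed meaning until one comparison is put first.

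The text allows several readings: a three-arm test, standard versus sham, standard versus eye closure, or any pairwise difference. A three-arm test rejects whenever any two arms differ, including when standard and sham are identical and only eye closure stands apart. A report of p < 0.05 on accommodative lag would then meet the stated threshold without showing anything specific to the standard exercise. With the comparison left open, it could also be chosen after the data are seen.

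**Working it through.** **Inputs from the protocol.** Three arms; estimated enrolment 180; significance level 0.05; ANCOVA or a nonparametric test. The enrolment comes with no effect size, SD, power or allocation ratio, so 180 cannot be reproduced and there is no plan figure to check first.

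**Assumptions.** Equal allocation, 180/3 = 60 per arm; two-sided tests; normal outcome with common SD. Differences d are in units of that SD (in an ANCOVA, the residual SD). The covariate is otherwise ignored. The values of d are illustrative, because the protocol gives no expected effect.

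**Step 1. Three-arm test when standard equals sham.** Let both exercise arms be better than eye closure by d. The arm means are d, d and 0, and their average is 2d/3. The noncentrality is

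λ = 60 × [2 × (d/3)² + (2d/3)²] = 60 × (6/9)d² = 40d².

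The test is F on 2 and 177 degrees of freedom, critical value 3.047.

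| d (SD) | λ | P(three-arm F significant) | P(standard vs sham significant) |
|---|---|---|---|
| 0.3 | 3.6 | 37% | 5% |
| 0.4 | 6.4 | 61% | 5% |
| 0.5 | 10.0 | 81% | 5% |

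A simulation of 200,000 trials gives 37.1%, 60.5% and 80.8% for the F test and about 5% for standard versus sham throughout. At d = 0.5, 76% of simulated trials have a significant three-arm test together with a non-significant standard versus sham test.

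**Step 2. Error rates when all three arms are equal.** These depend on which procedure is meant.

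| Procedure | Chance of at least one false claim |
|---|---|
| Three-arm F alone | 5% (simulated 4.9%) |
| Pairwise tests only after a significant F | 5% (simulated 4.9%) |
| Three pairwise tests at 0.05, no gate or adjustment | 12.2% |
| Two tests of standard against each control at 0.05, no gate or adjustment | 9.0% |

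For three tests, independence would give 1 − 0.95³ = 14.3%, and the upper bound is 3 × 0.05 = 15%. The simulated figure is lower because the comparisons share arms.

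**Step 3. What a single lead contrast can detect.** With 60 per arm, the detectable difference at 80% power and two-sided 0.05 is (1.960 + 0.842) × √(2/60) = 0.51 SD. Sharing alpha over three comparisons (0.05/3) raises it to (2.394 + 0.842) × √(2/60) = 0.59 SD. At a true difference of 0.5 SD, power is 78% at 0.05 and 63% at 0.05/3.

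**The case against.** **Contrast order and multiplicity are commonly left to a statistical analysis plan, and one may exist.** This stands for adjustment methods and follow-up tests. It does not cover the choice of the comparison that answers the trial's purpose. That is the primary hypothesis, and the protocol has a statistics section that sets the threshold and the test without it.

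**The text does not say that the three-arm test decides the trial.** Correct. ANCOVA can equally deliver a standard versus sham contrast at 0.05. The 37% to 81% therefore depend on the three-arm reading, and they mislead only if such a result is taken as an effect beyond sham.

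**The percentages might be read as false-positive rates.** They are not. In those scenarios eye closure really differs, so the F test is right to reject equality of all three arms. They are power figures.

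**A reader might infer that the plan runs at a 12% error rate, or that success may be claimed on the best of three pairwise tests.** The protocol describes no ungated pairwise testing. If pairwise tests follow only a significant three-arm test, family-wise error with three arms stays at 5%.

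**The arm labels already point to standard versus sham.** They do: the second arm is headed "Sham comparator: Nonstandardized eye exercise". But nothing in the Purpose, Outcome measures or Statistical analysis text makes it the lead.

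**Exercise versus no exercise is also a fair question for a nationwide school practice.** It is, and the Purpose does not exclude it. What favours sham is the protocol's own design: it calls that arm the comparator and claims blinding of subjects, and children told not to exercise cannot be blind to whether they were massaging.

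**Conclusion.** The point holds as a gap in the primary hypothesis: one threshold and one test family for three arms, with no comparison named to decide effectiveness. Under a three-arm reading, a significant result can come from eye closure alone, with probability 37%, 61% or 81% at 0.3, 0.4 or 0.5 SD. Those sizes rest on 60 per arm and on illustrative differences; the mechanism does not depend on either.

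The stronger conclusion, that type I error on the primary outcome more than doubles, is not supported. About 12% (three comparisons) or 9% (two comparisons with the standard arm) applies only to unadjusted, ungated pairwise tests, which the protocol neither prescribes nor rules out.

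The design can answer the acupoint question; the written rule does not require it to. This is a worthwhile and inexpensive correction, not a defect that invalidates the trial.

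**What to change.** In Statistical analysis, state that:

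1. The primary comparison for accommodative lag is standard versus sham, estimated as a contrast from the three-arm ANCOVA and tested at two-sided 0.05.
2. If it is significant, standard versus eye closure is tested at two-sided 0.05.
3. Sham versus eye closure, and the visual acuity and visual discomfort outcomes, are supportive and are reported with 95% confidence intervals.

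The chance of falsely claiming the standard exercise over sham is then 5% whatever happens in the eye-closure arm, and the first contrast gives up no alpha.

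The cost is a few sentences, with no new data, arms or participants. The real downside is that, if standard versus sham is not significant, no formal claim over eye closure can be made, even if that difference is large; it would be reported as an estimate with its interval.

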Appendix 2. Point table for evaluating the performance of eye exercises

Part I Press and knead BL2 (cuanzhu) (8 points)

|  | Item | Score | |
| --- | --- | --- | --- |
| Manipulation | Manipulate with thumb | Yes（1 point） | No（0 point） |
|  | Manipulate with fingertip | Yes（1 point） | No（0 point） |
|  | Manipulate in pressing and kneading | Yes（1 point） | No（0 point） |
|  | Manipulation diameter≦2 fingertip | Yes（1 point） | No（0 point） |
| Acupoint Location | At the median end of the eyebrow | Yes（1 point） | No（0 point） |
|  | In the supraorbital notch | Yes（1 point） | No（0 point） |
| Strength Effectiveness | Sense of sore (Qi) | Yes（1 point） | No（0 point） |
| Rhythm | One movement in a beat | Yes（1 point） | No（0 point） |

Part II Press and nip BL1 (jingming) (8 points)

|  | **Item** | **Score** | |
| --- | --- | --- | --- |
| Manipulation | Manipulate with index finger | Yes（1 point） | No（0 point） |
|  | Manipulate with fingertip | Yes（1 point） | No（0 point） |
|  | Manipulate in pressing and nipping | Yes（1 point） | No（0 point） |
|  | Manipulation diameter≦2 fingertip | Yes（1 point） | No（0 point） |
| Acupoint Location | In the depression slightly above the inner canthus | Yes（1 point） | No（0 point） |
|  | Nip bone instead of skin | Yes（1 point） | No（0 point） |
| Strength Effectiveness | Sense of sore (Qi) | Yes（1 point） | No（0 point） |
| Rhythm | One movement in a beat | Yes（1 point） | No（0 point） |

Part III Press and knead ST2 (sibai) (8 points)

|  | **Item** | **Score** | |
| --- | --- | --- | --- |
| Manipulation | Manipulate with index finger | Yes（1 point） | No（0 point） |
|  | Manipulate with fingertip | Yes（1 point） | No（0 point） |
|  | Manipulation diameter≦2 fingertip | Yes（1 point） | No（0 point） |
|  | Manipulate in pressing and kneading | Yes（1 point） | No（0 point） |
| Acupoint Location | Directly below the pupil | Yes（1 point） | No（0 point） |
|  | In the depression of the infraorbital foramen | Yes（1 point） | No（0 point） |
| Strength Effectiveness | Sense of sore (Qi) | Yes（1 point） | No（0 point） |
| Rhythm | One movement in a beat | Yes（1 point） | No（0 point） |

Part IV Press and knead EX-HN5 (taiyang),scrape orbit (16 points)

|  |  | **Item** | **Score** | |
| --- | --- | --- | --- | --- |
| Press and knead EX-HN5 | Manipulation | Manipulate with thumb | Yes（1 point） | No（0 point） |
|  |  | Manipulate with fingertip | Yes（1 point） | No（0 point） |
|  |  | Manipulate in pressing and kneading | Yes（1 point） | No（0 point） |
|  |  | Manipulation diameter≦2 fingertip | Yes（1 point） | No（0 point） |
|  | Acupoint Location | Between the lateral end of the eyebrow and the outer canthus | Yes（1 point） | No（0 point） |
|  |  | In the depression of the infraorbital foramen | Yes（1 point） | No（0 point） |
|  | Strength Effectiveness | Sense of sore (Qi) | Yes（1 point） | No（0 point） |
|  | Rhythm | One movement in a beat | Yes（1 point） | No（0 point） |
| Scrape orbit | Manipulation | Manipulate with index finger | Yes（1 point） | No（0 point） |
|  |  | Manipulate with second phalangeal joint | Yes（1 point） | No（0 point） |
|  |  | Manipulate in scraping | Yes（1 point） | No（0 point） |
|  |  | Scrape bone | Yes（1 point） | No（0 point） |
|  | Acupoint Location | On the bony structures of orbit | Yes（1 point） | No（0 point） |
|  |  | Include the whole orbit | Yes（1 point） | No（0 point） |
|  | Strength Effectiveness | Sense of sore (Qi) | Yes（1 point） | No（0 point） |
|  | Rhythm | One movement in 2 beat | Yes（1 point） | No（0 point） |

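### Appendix 2, Part IV: the two EX-HN5 location items conflict, so literal scoring stops at 39 of 40 and cannot tell the described site from the ST2 site

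*Protocol*

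**What the plan says.** Under Arms and Assigned Interventions, the protocol has two independent judges score each child's performance after training. Location is one of the assessed domains: "The assessment covered location, force, scope and frequency of the massage". The rule for passing is "Scores greater than 30/40 and differences between two judges less than 5 points were defined as qualified".

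Appendix 2 is the scoring sheet, made up of one-point yes/no items. In Part IV, the EX-HN5 block has two location items:

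- "Between the lateral end of the eyebrow and the outer canthus"
- "In the depression of the infraorbital foramen"

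The same second item appears in Part III for ST2. There its companion location item places the finger straight below the pupil.

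**The concern.** By the table's own anatomy, the infraorbital item belongs to a point under the pupil. The other EX-HN5 item puts the finger at the outer side of the eye. The two rows therefore ask for two different places in one manoeuvre.

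This matters because the sheet is operative. It produces the score behind the qualified rule, and location is what separates the two exercise arms: the standard arm is defined by accurate point positions and the sham arm by wrong ones. At one of the four named acupoints, a literal reading takes a point from a child at the described site and gives one for a site that the same table assigns to another acupoint. Two judges who read the row differently would also differ by a point for a reason unrelated to the child.

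**Working it through.** **Inputs.** Part totals come from the Appendix 2 headings: "Part I Press and knead BL2 (cuanzhu) (8 points"), "Part II Press and nip BL1 (jingming) (8 points"), "Part III Press and knead ST2 (sibai) (8 points"), and 16 points for Part IV, which holds EX-HN5 and orbit scraping. The cut-off comes from Arms and Assigned Interventions: "Scores greater than 30/40 and differences between two judges less than 5 points".

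**Step 1: reproduce the stated maximum.** Each of the five blocks (BL2, BL1, ST2, EX-HN5, orbit scraping) has 4 manipulation + 2 location + 1 strength + 1 rhythm = 8 items. The total is 5 × 8 = 40, which agrees with the headings (8 + 8 + 8 + 16 = 40) and with the denominator of the cut-off. No row is missing or broken, so the conflict does not come from text extraction.

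**Step 2: score EX-HN5 literally.**

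| Where the child massages during EX-HN5 | Eyebrow/canthus item | Infraorbital item | Location points |
|---|---|---|---|
| Site in the first item | 1 | 0 | 1 of 2 |
| ST2 site | 0 | 1 | 1 of 2 |

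The block maximum is 8 − 1 = 7 and the table maximum is 40 − 1 = 39. A sweep wide enough to cover both places does not rescue the point, because the same block has an item limiting the diameter of the movement to two fingertips. That item would be lost instead, and the ceiling would still be 39.

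**Step 3: margin to the cut-off.** If each judge's whole-number score must exceed 30, the lowest qualifying score is 31.

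- Table as written: 39 − 31 = 8 other points can be lost.
- With compatible items: 40 − 31 = 9.

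The protocol does not say whether the cut-off applies to each judge or to their mean. If it applies to the mean, 30.5 qualifies and the margins are 39 − 30.5 = 8.5 and 40 − 30.5 = 9.5. The loss is one point under either reading.

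**Step 4: how often one point could matter.** The protocol gives no score distribution. As an illustration only, assume each attainable item is passed independently with probability p, and compute the binomial probability of at least 31 passes.

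| Assumed p | 40 attainable items | 39 attainable items |
|---|---|---|
| 0.80 | 0.732 | 0.624 |
| 0.85 | 0.933 | 0.880 |
| 0.90 | 0.995 | 0.987 |
| 0.95 | about 1.000 | about 1.000 |

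The point matters for borderline performers and hardly at all for well-trained ones.

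**Step 5: judges.** If both read the row the same way, it adds nothing to their difference. If one scores it literally and the other as presumably intended, it adds 1 point against a limit of less than 5.

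**The case against.** The best case against raising this is that it is a clerical slip worth one point in 40, with no traced effect on any result. Most of that stands:

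- The protocol defines qualified but does not say what follows for a child who is not. The analysis is by intention to treat. A reader might infer that the row changes who is analysed, or biases the comparison of accommodative lag; the document supports neither.
- Children practise at least three times and are corrected until accurate before scoring, so scores well above 31 are plausible. The larger gaps in the illustration need pass rates of 0.80 to 0.85, which the protocol does not give.
- A reader might infer that a misplaced massage is rewarded. It is not, on balance: at the ST2 site the child gains the second item and loses the first. What fails is discrimination within the two-item sub-score.
- A reader might infer that the judges will disagree. That happens only if they read the row differently, and nothing in the protocol shows that they would.
- That the row was copied from ST2 is a fair guess from the identical wording, but only a guess. The Appendix 1 figure is not available in the text reviewed, so the intended item cannot be confirmed.

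None of this removes the contradiction, which is visible within Appendix 2 alone. Nor is it a matter to leave to a statistical analysis plan, since the protocol itself fixes the scoring sheet.

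**Conclusion.** The point holds in a limited form. The two EX-HN5 location items are incompatible as written. Under literal scoring the attainable maximum is 39 rather than 40, and the location sub-score for this acupoint is 1 of 2 at either site. The tolerance for other errors shrinks by one point, from 9 to 8 if the cut-off applies to each judge separately. The cut-off remains reachable, and no consequence for the primary outcome is shown.

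The conclusion rests on two assumptions: that judges score the row as printed, and that one finger position within the allowed diameter cannot be at both places, which follows from the table's own descriptions of EX-HN5 and ST2. It is a minor error in a working form, and worth correcting because it affects the measurement of location, the feature on which the exercise arms differ.

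**What to change.** Reconcile the second EX-HN5 location item in Appendix 2, Part IV with the item above it and with the Appendix 1 location figure. Keep two compatible one-point items, so that the total stays at 40 and the cut-off at more than 30 with no need to reset either. Give both judges the same corrected sheet.

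If scoring has already taken place, recheck only the children whose qualified status turns on that one point; wholesale rescoring is not warranted.

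The cost is one line of the scoring sheet and, at most, a short look at borderline scores.

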Appendix 3. Questionnaire for scoring visual discomfort

Please describe your feeling of eyes . Each question is rated on the following scale and attached a point value as follows:

Describe your feeling

(put √ on the number from 0-10)

|  | **no** | **slight** |  |  |  | **moderate** |  |  |  |  | **severe** |
| --- | --- | --- | --- | --- | --- | --- | --- | --- | --- | --- | --- |
| **Blur at near target** | 0 | 1 | 2 | 3 | 4 | 5 | 6 | 7 | 8 | 9 | 10 |
| **Blur at far target** | 0 | 1 | 2 | 3 | 4 | 5 | 6 | 7 | 8 | 9 | 10 |
| **Have difficulty keeping the target in focus when change the distance (from far to near/near to far)** | 0 | 1 | 2 | 3 | 4 | 5 | 6 | 7 | 8 | 9 | 10 |
| **Burning sensation** | 0 | 1 | 2 | 3 | 4 | 5 | 6 | 7 | 8 | 9 | 10 |
| **Eye dry** | 0 | 1 | 2 | 3 | 4 | 5 | 6 | 7 | 8 | 9 | 10 |
| **Soreness** | 0 | 1 | 2 | 3 | 4 | 5 | 6 | 7 | 8 | 9 | 10 |
| **Headache** | 0 | 1 | 2 | 3 | 4 | 5 | 6 | 7 | 8 | 9 | 10 |
| **Eye stained** | 0 | 1 | 2 | 3 | 4 | 5 | 6 | 7 | 8 | 9 | 10 |
| **Sensitive to light** | 0 | 1 | 2 | 3 | 4 | 5 | 6 | 7 | 8 | 9 | 10 |
| **Eye discomfort** | 0 | 1 | 2 | 3 | 4 | 5 | 6 | 7 | 8 | 9 | 10 |
